The study procedure will be explained orally to the participants, and thumbprints will be obtained from all the eligible participants before any assessment or intervention. Apart from that, for participants aged from 15 to 18 years old, the research team will obtain oral assent with thumb print, and a consent form will be signed by their legal guardian for their willingness to allow their children to join this research program before the start of any assessment. Participation in this project will be voluntary, and participants can withdraw from the study anytime. The data will be confidential to protect the privacy of the participants. All data will be kept locked and secured, and access will be restricted to only the related research staff. Independent research assistants, without knowing group allocation, will administer the questionnaires orally to each participant and note down the answers in the hard copy. In case of doubt, the chief investigator will clarify the concerned point. Paramedical staff will withdraw blood in a standard hygienic environment. The study and ethical clearance are conducted according to the Declaration of Helsinki guidelines.

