This study is a multi-centered, assessor-masked, three-armed RCT. A convenient sampling method will be adopted for the selection of participants. They will undergo the ophthalmologic visual acuity test for screening. Eligible participants will be randomly assigned to either MY, PE, or wait-list control group through computer software (Randomizer) based on gender, age, and severity of vision loss, in which each group contains the same proportion of the factors mentioned above.

The intervention will be for eight weeks (one hour/day, five days a week), and a follow-up assessment will be carried out six months after the completion of the intervention. The study contains three times evaluations in which the baseline assessment (T0) will be before group division. Post-intervention assessment (T1) will be at the end of the intervention for eight weeks. Follow-up assessment (T2) will be six months after the completion of the intervention. The principal researcher will make unannounced weekly visits to the intervener's class to assess the adherence, consistency, and quality of the intervention. In each classroom, MY or PE, two teaching assistants will support the main instructor in conducting the classes to minimize the risk of injury, such as ankle and knee injuries for the participants.

Randomization method

Stratified randomization will be employed to randomly assign participants based on three factors: age, gender, and the severity of visual impairment. This approach aims to reduce potential confounding effects and enhance the validity of the results.

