Participants will first be categorized by gender into two groups: male and female. Within each gender group, participants will be further subdivided into two age categories: adolescents (15-17 years) and young adults (18-25 years). Each of these subcategories will then be divided according to the severity of visual impairment: 1) Mild visual impairment: visual acuity worse than 6/12 but better than or equal to 6/18); 2) moderate visual impairment: visual acuity worse than 6/18 but better than or equal to 6/60); 3) severe visual impairment: visual acuity worse than 6/60 but better than or equal to 3/60); 4) Blindness visual impairment: visual acuity worse than 3/60 or a corresponding visual field loss to less than 10 degrees in the better eye with the best possible correction) [47]. Participants in each subgroup at this third level will have their names entered into a computer software program called Randomizer for shuffling. After shuffling, participants will be randomly allocated to one of three groups: the mindfulness-based yoga group, the physical exercise group, or the wait-list control group. The allocation ratio will be 1:1:1. 

Participants recruitment

People with moderate-to-severe VI will be recruited through two primary sources, namely two non-profit rehabilitation organizations (NGOs): the Samarthanam Trust for the Disabled and the Devnar Foundation for the Blind. The sample population will be drawn from the two above-mentioned NGOs by adopting the random sampling method. The intervention will be conducted across multiple sites nationwide, as participants with VI are taken care of by various branches of these two NGOs.

Potential participants will be approached through coordinated efforts with the institutions for the blind. Information sessions will be organized and conducted with the authorization of the governing body and instructors to explain the study's objectives, procedures, and potential benefits. Detailed written materials will be provided, and verbal explanations will be given to ensure comprehension. Participants will have the opportunity to ask questions and discuss any concerns. Informed consent will be obtained from each participant before inclusion in the study, ensuring they fully understand their involvement and the study's requirements. The research will not involve professors or instructors of the visually impaired participants to avoid any perception of obligation among students to participate.

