Physical well-being - 30-second Chair Stand Test (30 CST): The 30-second Chair Stand Test (30 CST), or the 30-second Sit-to-Stand Test, is primarily designed for older adults to assess leg strength and endurance [75]. It counts the maximum number of repetitions between standing up and sitting down within 30 seconds with participants’ arms crossed in front of the chest in an armless, 17-inch-high, padded chair against a wall to maintain stability. It is a part of the Fullerton Functional Fitness Test Battery. However, it has also been used to test the population with VI for the same purpose since they tend to have less lower limb strength due to a lack of motor activity [76]. It is a simple and effective tool that provides a reliable and valid indicator of lower body strength, which is an essential factor in maintaining functional ability. The previous study has shown excellent inter-rater reliability (ICC value 0.94) and intra-rater reliability (ICC value 0.91) and has demonstrated good construct validity in assessing physical performance [77]. 

Social well-being - Multidimensional Scale of Perceived Social Support (MSPSS): The MSPSS is a self-explanatory 12-item inventory. It has good internal reliability, and test-retest reliability as well as moderate construct validity. The reliability of the whole scale was 0.88, indicating good internal consistency for the scale. The subscales (family, friends, significant other) representing the different sources of social support are strong in factorial validity. High levels of perceived social support are associated with low levels of depression and anxiety [78]. Individuals with VI tend to be socially isolated, resulting from limitations in understanding body language during communication [16].

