Given the attrition and missing data in the experiment, the research team will account for a 20% attrition rate and closely monitor the progress of the trial with the aim in mind. To minimize attrition and missing data, it will be emphasized to both research team members and participants that full and complete participation in the intervention is crucial, regardless of the treatment assignment. Follow-ups will be scheduled at participants' convenience, with the assistance of two NGOs, and participants will receive WhatsApp reminders one day before each event.

To handle missing data, we will implement diligent monitoring and provide thorough explanations of study procedures to ensure a positive research experience. Highlighting the altruistic reasons for participation, we will elucidate the significance of maintaining involvement for all the participants. At the end of each follow-up, assessors will explain performance assessments and relevant health concerns to participants [86]. To achieve it, the research team will keenly supervise the whole procedure. The research team will contact participants through the authorities of the two NGOs for follow-up arrangements and conduct follow-up data collection at the participants' convenience.

Additionally, we will identify potential confounding factors and implement controls to mitigate their impact on the study results. This may include adjusting for baseline characteristics, using stratified randomization, and employing statistical techniques such as multivariable regression analysis to control for these factors in the data analysis.

Ethical consideration

This study trial has obtained approval from the institutional ethics committee (IEC) with the Institutional Ethics Committee Clearance Certificate Reference Number: RES/IEC-SVYASA/203/2021. It has been registered in the Clinical Trial Registration of India (CTRI) with the registration number of WHO The Clinical Trials Registry - India: CTRI/2021/08/035853.

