## Results

Data will be collected and extracted using the standard procedure. The appropriate statistical test will be conducted to analyze the above-mentioned variables using SPSS V. 22.0 software (IBM Inc., Armonk, New York). To find out the differences between groups, an ANOVA test will be adopted; to check within-group changes, a repeated measures ANOVA will be used. The findings will be released subsequent to the study of the data.

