The strengths of this research are: 1) subjective psychological questionnaires correlating with objective, evidence-based assessment will strengthen the study design; 2) multiple centers with a large sample size in different geographical areas will support generating the findings of this research; and 3) a three-group study design will enhance the strength of the study. The active control group (PE group) will be compared with the experimental group (MY group) to discover the potential mechanisms of yoga, especially the effects of mindful awareness on psychological well-being. The wait-list control group will be compared with the other two to reveal the significance of either type of physical activity contributing to general well-being.

Limitations

Potential limitations and their related strategies need to be acknowledged. Subject dishonesty might happen during the interview process to protect one's privacy and social identification, as they might appear to have prosocial behaviors toward interviewers. To ameliorate the effects of bias, the interviewers will inform the participants that private information will be kept confidential, and the interview will be in the form of a one-on-one session. It is crucial to keep in mind that despite the study's design using numerous centers and a sizable sample size from various geographic regions, regional-specific factors like cultural differences, resource accessibility, and customs may still have an impact on the findings. However, in this study, stratified randomization will be adopted to minimize the potential effects of confounding factors such as location, population, educational and cultural differences where the research will take place. Since each center shares certain similarities in terms of setting, such as food habits, living standards, teaching methods, and cultural background, it is reasonable to expect that various confounding factors will have the minimum effects on the results. Additionally, this study will investigate the evaluation and implementation of the MY or PE protocol. However, social support will not be considered as one factor for randomization. Therefore, it will be possible if there will be varying levels of social support among the three groups. Dropouts and missing data may also pose a risk to internal validity. The strategy to reduce the dropout rate has been discussed previously in the section named "attrition and missing data".

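### Allocation is stratified by gender, age band and severity, but the named between-group test is a plain ANOVA and baseline adjustment is left optional with no covariates named

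*Protocol article*

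**What the plan says.** **Allocation.** The protocol article, Randomization method, states: "Stratified randomization will be employed to randomly assign participants based on three factors: age, gender, and the severity of visual impairment". Gender has two levels. For age, "participants will be further subdivided into two age categories: adolescents (15-17 years) and young adults (18-25 years". Severity has four levels (mild, moderate, severe, blindness). "The allocation ratio will be 1:1:1".

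**Analysis.** The Results section says: "To find out the differences between groups, an ANOVA test will be adopted; to check within-group changes, a repeated measures ANOVA will be used". The abstract names the same two tests. Neither place mentions a stratum or covariate term.

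**Adjustment.** The section Attrition and missing data says that confounders will be identified and controlled, and continues: "This may include adjusting for baseline characteristics, using stratified randomization, and employing statistical techniques such as multivariable regression analysis". It does not say which characteristics or which outcomes. It also lists stratified randomisation as one possibility, although the Randomization method section has already fixed it.

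**Social support.** The Limitations section states that social support is not a randomisation factor and adds: "Therefore, it will be possible if there will be varying levels of social support among the three groups". It names no adjustment. The outcome section on the Multidimensional Scale of Perceived Social Support (MSPSS) says: "High levels of perceived social support are associated with low levels of depression and anxiety". Table 1 schedules MSPSS at T0, T1 and T2.

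**Timing of T0.** The Design section places the baseline assessment before group division. Table 1 shows T0 under its post-allocation heading.

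**The concern.** Stratified allocation makes the arms nearly identical on the three factors. Any part of HADS that depends on them then adds little to the true sampling error of an arm difference. A plain ANOVA still leaves that part in the residual variance, so its standard error describes a trial that was not stratified.

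The stake is precision. Intervals come out wider than they need to be, the test runs below its nominal 5%, and the power that stratification could provide is not collected. This matters most for the second hypothesis, yoga superior to exercise, which compares two active arms.

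There is also a matter of discipline. Adjustment is optional and no covariate is named, so this document does not exclude choosing the model after the data are seen.

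**Working it through.** The plan gives no figure on this point, so there is none to reproduce.

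**Inputs from the protocol article**
- 36 evaluable per arm, so 3 × 36 = 108 in total (Sample size)
- 20% attrition (Sample size)
- 1:1:1 allocation (Randomization method)
- 2 × 2 × 4 = 16 strata as listed, or 2 × 2 × 3 = 12 if the mild level stays empty, since eligibility requires moderate-to-severe impairment

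**Assumed, because the documents do not give it:** R2, the share of variance in the analysed outcome explained by the three factors, at 0.05, 0.10 and 0.20, with 0 as the lower limit.

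**Step 1. Standard error, full balance.** The plain ANOVA reports a variance proportional to 1. The true variance is proportional to 1 − R2. The ratio of reported to true standard error is 1/√(1 − R2).

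**Step 2. Standard error, balance loosened by attrition.** If 20% are lost at random, the stratum part of each arm mean is a random 80% sample from a balanced set. It keeps a fraction 1 − 0.8 = 0.2 of its variance. The true variance is proportional to (1 − R2) + 0.2·R2 = 1 − 0.8·R2, and the ratio is 1/√(1 − 0.8·R2).

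**Step 3. Type I error of a two-arm comparison, full balance.** With 36 + 36 − 2 = 70 degrees of freedom the 5% critical value is 1.994. The true error is the two-sided t tail beyond 1.994/√(1 − R2). The tail must come from the t distribution as well: a normal tail gives 4.6% at R2 = 0, where the answer is 5%.

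| R2 | SE excess, full balance | SE excess, 20% attrition | Scaled critical value | True type I error |
|---|---|---|---|---|
| 0 | 0% | 0% | 1.994 | 5.0% |
| 0.05 | 1/√0.95: 2.6% | 1/√0.96: 2.1% | 2.046 | 4.4% |
| 0.10 | 1/√0.90: 5.4% | 1/√0.92: 4.3% | 2.102 | 3.9% |
| 0.20 | 1/√0.80: 11.8% | 1/√0.84: 9.1% | 2.230 | 2.9% |

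**Step 4. Simulation.** 4000 runs per setting, 108 evaluable, 1:1:1 in blocks within 12 strata, no attrition.
- At R2 = 0.20 the plain ANOVA reported a mean standard error of 0.236 against a true 0.212. The model with the three factors reported 0.211 against 0.210.
- The overall three-arm F test without the factors rejected a true null in 4.0% / 3.9% / 2.3% of runs at R2 = 0.05 / 0.10 / 0.20. With the factors it rejected in 4.6% / 5.1% / 5.0%. The Monte Carlo standard error is √(0.05 × 0.95/4000) ≈ 0.3 points.
- The treatment estimate showed no bias beyond simulation error in any setting.
- With one arm shifted by an assumed 0.7 SD, adding the factors raised power from 87.3% to 89.7% (R2 = 0.10) and from 88.3% to 93.1% (R2 = 0.20).

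**Step 5. Social support.** For a factor not used in allocation, the chance standardised difference between two arms of 36 has SD √(2/36) = 0.236, so a 95% range of ±1.96 × 0.236 = ±0.46. In the simulation, with an assumed R2 of 0.10 for the strata and a further 0.15 for a T0 covariate such as MSPSS, power at the same 0.7 SD shift rose from 87.7% (plain ANOVA) to 94.2% (strata and covariate). The T0 value of HADS was not in that model. With it included, MSPSS would probably add less.

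**The case against.** **Adjustment is foreseen.** The attrition section commits to identifying and controlling confounders, and gender, age and severity are baseline characteristics. This stands against the reading that the analysis ignores the factors, which a reader might infer from the Results section alone. The documents show only that the two sections are not aligned.

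**Covariate lists belong to the analysis plan.** This is a condensed article and no analysis plan is shown. Silence on covariates would be no finding. Here, however, the article names a test, and that test does not use the stratification the same article fixes. The objection limits the point to an improvement of a stated method.

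**The size is not known.** The documents give no R2, and with R2 near 0 nothing is lost. The Results section does not say whether scores or changes are compared. If changes are, a constant effect of the factors on HADS level cancels and the relevant R2 may be small. This stands, and the figures are conditional on it.

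**Nothing is biased.** A reader might infer a false-positive risk, or that the conceded imbalance in social support distorts the comparison. Neither follows. The plain ANOVA errs on the conservative side. The three stratified factors are balanced by design, and any social-support imbalance arises by chance under randomisation. Nor would a T0 covariate remove it fully, since MSPSS is measured with error (the article gives a reliability of 0.88).

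**Conclusion.** The point holds as a mismatch between design and named analysis, with adjustment left optional and unspecified. The consequence is conservative and modest: standard errors up to about 12% too wide and a true type I error down to about 2.9% at R2 = 0.20, and no loss at R2 = 0. These figures assume that the factors predict the variable actually analysed and that balance survives to the analysis. Random attrition of 20% cuts the excess to about 9% at the same R2. The documents do not support a claim of bias, of inflated false positives, or of unconditionally wide intervals. The point is still worth acting on, because the remedy is nearly free.

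**What to change.** 1. In the Results section, name one between-group model for HADS with arm, gender, age band and severity as used at randomisation, plus the T0 value of the outcome. State that empty severity levels are merged.
2. T0 MSPSS may be added as a pre-specified covariate. Describe the purpose as precision against chance imbalance, not correction of bias.
3. Align the other sections. The attrition section should refer to this model instead of listing options, and the Limitations section should say whether social support is adjusted for.
4. Reconcile the post-allocation heading over T0 in Table 1 with the Design section, so that T0 values are clearly baseline covariates.

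Cost: gender 1, age band 1, severity 2 (three occupied levels) and T0 outcome 1 make five degrees of freedom, or six with MSPSS, out of 108 − 3 = 105. The change takes a few sentences and no new data.

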## Introduction

People with visual impairment (VI) face a higher risk of psychological distress, which affects their multidimensional health aspects [1]. The mortality rate among the visually impaired is much higher than that of normally sighted people [2]. Visual impairment, characterized by low vision or blindness, is a functional limitation of the eyes. At least 2.2 billion people worldwide are visually impaired, and this is gaining growing concern in the development of public health policies [3]. Based on global population growth and increased life expectancy, it is estimated that global blindness will triple and moderate-to-severe VI will double by the year 2050 [4]. Though VI affects hundreds of millions globally, 90% of those with VI live in low- and middle-income countries [5]. India contributes 8 million people with blindness and 62 million with VI to the global population [6]. 

Loss of vision affects various aspects of life, such as reduced physical activities, unintentional injuries, loneliness, disturbed sleep, and low self-esteem [7-12]. Compared with the general population, people with VI are at a higher risk of experiencing psychological distress, such as anxiety and depression [13,14]. In return, the accumulated stress can lead to more vision loss [15]. Various factors contribute to psychological distress in the visually impaired, such as poor social communication, compromised daily role functions, and self-care capacities [16-19]. In addition, they face a higher chance of unemployment and more stress from family responsibilities and marriage expectations than their sighted peers [20-22]. Psychological distress in VI induces fatigue, low self-esteem, caregiver distress, and socioeconomic burden at large [23-26]. In addition, people with VI, especially those with no perception of light, tend to experience poorer sleep quality than the sighted due to the desynchronized rhythm of melatonin secretion [11]. Sleep disturbance is a mediating factor in mental health, and sleep management has been used as an effective strategy to treat mental disorders [27].

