The primary outcome will be the level of psychological distress assessed using the Hospital Anxiety and Depression Scale (HADS). Additionally, psychological well-being will be evaluated using the Oxford Happiness Questionnaire (OHQ), while psycho-hormonal well-being will be examined through the analysis of biomarkers such as dopamine, serotonin, cortisol, endorphin, and melatonin. The secondary outcomes will encompass psychophysiological well-being assessed by heart rate variability (HRV), electrocardiograph (ECG), galvanic skin resistance (GSR), respiratory rate (RR), and electromyography (EMG). Functional balance, mobility, and fall risk will be evaluated using the Time Up and Go test (TUG). Strength and endurance will be measured using the 30-second Chair Stand Test (30 CST). Social well-being will be assessed using the Multidimensional Scale of Perceived Social Support (MSPSS), while the Spiritual Well-being Scale (HWS), health-related quality of life will be measured by the Vision Quality and Life Index (VisQoL), and sleep quality will be assessed using the Pittsburgh Sleep Quality Index (PSQI).

Primary Outcomes

Psychological well-being in terms of anxiety and depression will be measured by the Hospital Anxiety and Depression Scale; happiness will be measured by the Oxford Happiness Questionnaire; and its related hormonal changes will be measured by dopamine, serotonin, endorphin, cortisol, and melatonin.

Hospital Anxiety and Depression Scale (HADS): Psychological well-being in terms of anxiety and depression will be measured by the HADS. This scale has been suggested for the population with VI [57]. The HADS consists of two subscales: anxiety and depression. Each subscale consists of seven items, each rated on a four-point Likert scale ranging from 0 to 3. A score of eight or above on each subscale and 15 or above on the full scale represents a clinically relevant cut-off value to detect anxiety and depressive symptoms. The English version of HADS has demonstrated satisfactory validity and reliability, with a Cronbach's alpha of 0.80 for the depression subscale and 0.81 for the anxiety subscale. The correlations between the two subscales, anxiety (HADS-A) and depression (HADS-D), varied from 0.40 to 0.74 (mean of 0.56). An optimal balance between sensitivity and specificity was achieved when the score reached eight or above on both HADS-A and HADS-D [58,59]. 

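### Stratification does not balance the arms on light perception, which the Introduction links to melatonin and sleep; recording it and adjusting for it would be a cheap gain in precision

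*Protocol article*

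**What the plan says.** All references are to the protocol article.

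- **Randomization method.** Stratification will "randomly assign participants based on three factors: age, gender, and the severity of visual impairment". There are two gender levels, two age levels and four severity levels. The last severity level is "Blindness visual impairment: visual acuity worse than 3/60 or a corresponding visual field loss to less than 10 degrees". Within the resulting subgroups, "The allocation ratio will be 1:1:1".
- **Introduction.** It says of people with visual impairment that they, "especially those with no perception of light, tend to experience poorer sleep quality than the sighted due to the desynchronized rhythm of melatonin secretion". It adds that sleep disturbance mediates mental health.
- **Primary Outcomes.** Alongside HADS and OHQ, "its related hormonal changes will be measured by dopamine, serotonin, endorphin, cortisol, and melatonin". The PSQI is a secondary outcome.
- **Design and Table 1.** Biomarkers and PSQI are measured at T0, T1 and T2. The Design section says that "the baseline assessment (T0) will be before group division". Table 1 appears to place T0 under its post-allocation heading, but T0 precedes the intervention in both places.
- **Attrition and missing data.** On control of confounding: "This may include adjusting for baseline characteristics, using stratified randomization, and employing statistical techniques such as multivariable regression analysis". This is worded as an option and names no variable.
- **Results.** Between-group differences are tested by ANOVA and within-group changes by repeated measures ANOVA. No covariate is named.

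The article does not mention light perception as a recorded item, a stratum or a covariate.

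**The concern.** Stratification is meant to limit confounding. For melatonin and sleep, the one visual characteristic that the protocol itself ties to the outcome is whether light is perceived at all. The severity factor stops at 3/60, or a field under 10 degrees, and puts everyone beyond that in one class. The number of participants without light perception in each arm is therefore left to chance.

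If light perception matters for these two outcomes as the Introduction suggests, an unadjusted ANOVA carries its variance as noise. In an unlucky draw, the mindfulness-based yoga (MY) versus physical exercise (PE) difference in melatonin or PSQI would be partly a difference in case mix, and nobody could tell unless light perception had been recorded.

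**Working it through.** The plan gives no figure on this point to reproduce. Only the planned 44 per arm is used. How that sample size was derived is a separate matter, and nothing here depends on it.

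**Inputs**

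- From the documents: 44 per arm, three arms, 1:1:1 allocation, and 2 × 2 × 4 = 16 strata, or 132/16 = 8.25 participants per stratum on average.
- Assumed, because the documents give no shares: 30% to 90% of participants in the blindness class, and 20% to 60% of those without light perception.
- Assumed, because the documents give no effect: absence of light perception shifts the outcome by 0.8 residual SD.

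**Step 1: chance imbalance.** Let the blindness class hold n per arm, N = 3n in all, of whom K lack light perception. With arms balanced on the class but not within it, the difference in counts between two arms has variance 2K(N − K) / [3(N − 1)].

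- Lowest case, n = 13, K = 8: 2 × 8 × 31 / (3 × 38) = 4.35. The SD is 2.09, or 2.09/44 = 4.7 points.
- Middle case, n = 26, K = 31: 2 × 31 × 47 / (3 × 77) = 12.6. The SD is 3.55, or 8.1 points.
- Highest case, n = 40, K = 72: 2 × 72 × 48 / (3 × 119) = 19.4. The SD is 4.40, or 10.0 points.

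A simulation of 20,000 allocations agrees to rounding:

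| Blind per arm | Without light perception | SD of MY − PE share | P(≥10 points) | P(≥15) | P(≥20) |
|---|---|---|---|---|---|
| 13 | 8 of 39 | 4.7 points | 3% | about 0% | about 0% |
| 26 | 31 of 78 | 8.1 points | 21% | 7% | 1% |
| 40 | 72 of 120 | 9.9 points | 30% | 14% | 5% |

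The mean difference is zero in every scenario.

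**Step 2: effect on an arm difference.** A 10-point imbalance shifts it by 0.10 × 0.8 = 0.08 SD, and a 15-point imbalance by 0.15 × 0.8 = 0.12 SD.

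**Step 3: compare with the standard error (middle case).**

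- With light perception accounted for: √(2/44) = 0.213 SD.
- With its chance imbalance added: √(0.0455 + (0.8 × 0.081)²) = 0.223 SD. The simulated value over 10,000 trials is 0.221 SD.

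The standard error is therefore 4% to 5% larger than it need be.

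**Step 4: validity (middle case).** In the same 10,000 trials the unadjusted three-arm ANOVA rejected a true null in 4.6% of cases (nominal 5%), with mean bias of about 0.

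**The case against.** The case for leaving the plan alone is strong in several respects.

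- **No promise is broken.** The Design section promises equal proportions of gender, age and severity only. Every trial leaves some prognostic factor unstratified. This stands: the point is an improvement, not an error.
- **The article is condensed.** What the ophthalmology test records, and which covariates are used, may be set out in a full protocol or analysis plan that is not shown. This stands too, so silence here is no proof that light perception goes unrecorded. What the article does fix are the stratum boundaries and an ANOVA as the between-group test.
- **Baseline values help.** Melatonin and PSQI are measured at T0 and the impairment is early-onset, so a lasting effect of absent light perception should largely show at T0. Using the T0 value would absorb part of any imbalance. For melatonin it may absorb less: Data collection describes morning blood sampling between 6 and 9 am, and with a desynchronised rhythm such samples need not catch the same phase at each assessment. That is an inference from the protocol's stated mechanism. In any case, baseline adjustment is only an option in the text.
- **Splitting the stratum has a price.** A fifth severity level gives 20 cells and 132/20 = 6.6 participants per cell, and would change the scheme after 62 participants had been recruited. Not splitting is defensible.

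A reader might also infer that absent light perception is the main determinant of these outcomes. The Introduction offers one background sentence, about visually impaired people in general and this subgroup especially, and gives no effect size. It makes no link to cortisol.

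**Conclusion.** The point holds as a minor one. The severity factor does not balance the arms on light perception, and the stated analysis does not adjust for it, although the protocol's own rationale ties it to melatonin and sleep. Under the assumed shares, the between-arm difference in share has an SD of about 5 to 10 points, and a gap of 10 points or more between MY and PE has a probability of 3% to 30%. With an assumed 0.8 SD effect, such a gap of 10 points moves the comparison by 0.08 SD, well within a standard error of about 0.22 SD.

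Two stronger readings are not supported:

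- **That the arms are confounded or the test invalid.** Randomisation balances light perception in expectation, and the simulated type I error is nominal.
- **That imbalance could account for 40% to 50% of the planned effect.** That figure needs a 1 SD shift, half of the blind lacking light perception (the share that maximises the variance) and the 95% extreme of the draw. It then divides by 0.4, for which Sample size states no metric and which concerns overall well-being, not melatonin or PSQI.

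The point also presupposes that blind participants are enrolled. Inclusion and exclusion criteria admit moderate-to-severe impairment, the objectives add blindness, and Randomization method has strata for both mild impairment and blindness. These passages must be reconciled.

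**What to change.** - Record light perception (present or absent) at the ophthalmology test already scheduled in Table 1. If it is already recorded, say so. For participants already allocated, take it from the screening record or ask about status at entry at the next visit, through a masked assessor.
- Report it by arm with the baseline characteristics.
- Prespecify light perception and the T0 value as covariates in the between-group comparisons of melatonin and PSQI, in place of an unadjusted ANOVA.
- Reconcile the eligibility and stratum descriptions for mild impairment and blindness.

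The strata need not change, and no subgroup analysis is needed. The cost is one yes/no field and one degree of freedom for light perception, with one more for the T0 value, which the article already mentions as a possible adjustment.
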